### **1.7.1 Study Population and Sample Size Justification**

A total of 45 non-transplant candidates and/or transplant candidates who agree to defer transplant will be enrolled. The sample size is selected to allow for a collection of sufficient data for evaluation of sCR and MRD rates at the end of 8 cycles, which assumes that we may not have successful MRD evaluation in up to 25% of patients (primary endpoint), and that up to 15% of transplant candidates may change their mind and want to proceed to transplant, both based on historical experience in our prior KRd studies and based on historical rates of sCR from KRd study without ASCT (or deferred transplant) of 30% at the end of 8 cycles, and preliminary rates of sCR and MRD by NGS at the end of Cycle 8 of 69% and 66%, respectively (both to be updated at ASH 2016).

## **1.8 Assessment for Response**

Response will be determined according to the IMWG response criteria for multiple myeloma (2006). Disease assessment for response will include serum protein electrophoresis (SPEP), urine protein

electrophoresis (UPEP), serum free light chains (SFLC), Hevylite test, and immunoglobulins (Igs). Bone marrow procedures should be completed at the time of suspected complete response. Additionally, for subjects who have a plasmacytoma or disease measured by imaging at baseline, plasmacytoma evaluations and radiographic imaging should be completed as per standard of care and in accordance with IMWG response criteria for multiple myeloma. Patients who achieve SD, PR, or CR will continue therapy until disease progression. Patients with disease progression will discontinue the treatment regimen and be removed from protocol.

## **2 OBJECTIVES**

### **2.1 Primary Objective**

The primary objective of this study is to evaluate the rate of sCR response as well as the rate of MRD-negative disease by NGS at the end of 8 cycles of D-KRd.

### **2.2 Secondary Objectives**

Secondary objectives include characterization of efficacy variables:

- Rate of MRD by next generation gene sequencing (NGS) by clonoSEQ® (Adaptive Biotechnologies) at the end of Cycle 8 and at the end of Cycle 24, and then yearly for as long as no PD up to 2 years.
- Duration of response (DOR), progression free survival (PFS), time to progression (TTP), and overall survival (OS).
- Overall response rate defined as partial response or better (>PR) including the rate of VGPR or better (>VGPR) and near-complete response or better (sCR/CR/nCR) across entire treatment in high-risk and low-risk patients at indicated time points and as best response.
- Safety and tolerability of combination of D-KRd.

### **2.3 Exploratory Objectives**

The exploratory objectives of this study are to conduct GEP, proteomics, RNASeq, and gene sequencing studies on pre-treatment patient samples to evaluate the correlation between treatment outcome and pre-treatment patient profile.

### **3 STUDY ENDPOINTS**

#### **3.1 Primary Endpoints**

The evaluation of sCR and MRD-negative rates at the end of 8 cycles will be achieved by measuring the time to sCR response and MRD-negative result from start of treatment as defined by IMWG criteria.

#### **3.2 Secondary Endpoints**

Secondary endpoints include the following:

- Determining the correlation between sCR response and MRD status at Cycles 8 and 24 and then yearly for as long as no PD up to 2 years as well as PFS.
- Duration of response (DOR), progression free survival (PFS), time to progression (TTP), and overall survival (OS).
- Safety and tolerability of combination of D-KRD measured by frequencies of adverse events, serious adverse events, and adverse events leading to discontinuation of study treatment.

#### **3.3 Tertiary/Exploratory Endpoints**

The exploratory objectives of this study are to conduct GEP, proteomics, RNASeq, and gene sequencing studies on pre-treatment patient samples to evaluate the correlation between treatment outcome and pre-treatment patient profile.

### **4 INVESTIGATIONAL PLAN**

#### **4.1 Overview of Study Design and Dosing Regimen**

This study will be a multi-center, open-label, phase 2 study, enrolling subjects with newly diagnosed MM requiring systemic chemotherapy. All dosing schedule is based on 28-day cycles. Subjects will receive treatment until disease progression or unacceptable toxicity (whichever occurs first).

Enrolled subjects will initially receive lenalidomide at 25 mg per dose (see below if previously unable to tolerate 25 mg) on Days 1-21. Carfilzomib will be dosed at 20 mg/m^2 on Days 1 and 2 and 36mg/m^2 thereafter (Days 8,9,15, and16). Alternative escalation will be allowed on Cycle 1 if the treating

investigator considers it necessary as follows: 20 mg/m^2 on Days 1 and 2 escalated to 27 mg/m^2 on Days 8 and 9, and then to 36 mg/m^2 on Days 15 and 16. Daratumumab will be administered by subcutaneous injection, provided as a fixed-dosed of 1800 mg and 30,000 units hyaluronidase per 15 mL (120 mg and 2,000 units/mL) for all cycles. The injection will be given by manual push over 3 to 5 minutes in the abdominal SC tissues in left/right locations, alternating between individual doses. Dexamethasone will be dosed at 40 mg PO per week for subjects < 75 years and 20 mg PO per week for subjects ≥ 75 years during Cycles 1-4. Dose modifications will be mandated based on aggressive schedule of dose modification for toxicities as per specific guidelines. Otherwise, patients will continue at their best tolerated dose of lenalidomide on Days 1-21 and their best tolerated dose of carfilzomib on Days 1, 2, 8, 9, 15, 16 in Cycles 1-4 and Days 1, 2, 15, 16 in Cycles 5-8.

All subjects will have monthly clinic visits for disease assessments. Treatment will continue on protocol for up to 24 months or if carfilzomib, lenalidomide and daratumumab are permanently discontinued. If dexamethasone is discontinued due to toxicity, carfilzomib, lenalidomide and daratumumab may be continued if tolerated without dexamethasone. Toxicity will be graded using the National Cancer Institute Common Terminology Criteria for Adverse Events version 4. Patients who complete 24 cycles will then continue single-agent lenalidomide at best tolerated dose (up to 25 mg) in 28-day cycles. This regimen will continue until there is progression of the disease or the toxicities require discontinuation of the drug.

Minimal residual disease analysis will be performed using NGS. MRD will be assessed in all bone marrow samples at the beginning of the study (after Cycles 8 and 24), yearly until progression and at any time a bone marrow biopsy is completed to assess response for suspected CR. If a CR is suspected after Cycle 8, a bone marrow biopsy and MRD testing will be completed at Cycle 12 and/or 18 to confirm. From the time CR is established, MRD analysis should continue at 12-month intervals from randomization up to 5 years in patients with ongoing sCR. The MRD samples will be evaluated by Adaptive Biotechnologies using LymphoSIGHT® platform after isolation of DNA at the University of Chicago site. For this purpose (and to establish a baseline), sites will be required to provide unstained pre-treatment slides to assess MRD status by Adaptive Biotechnologies. MRD analysis will be used only for assessment of treatment response at specified timepoints, and not for decision-making purposes.

Treatment responses will be assessed by serum free light chains (SFLC), Hevylite test, quantitative immunoglobulin levels (Igs), and serum and urine monoclonal protein starting at Cycle 2 Day 1 and at the

beginning of each subsequent cycle. Subjects with stable disease or better will continue treatment until disease progression or the development of unacceptable toxicities. All patients will then undergo a final visit (end of treatment visit).

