|  | 
 
- Cycle 1: Days 8, 9, 15, and 16: 36 mg/m^2
 
 
*Alternatively, intermediate dose escalation (to 27mg/m^2 on Days 8, 9 of Cycle 1) will be allowed at the treating physician's discretion.
 
 
- Cycle 2-8 36 mg/m^2 (or last best tolerated dose) of carfilzomib on Days 1, 2, 8, 9 and 15, 16
 
- Cycle 9-24: 36 mg/m^2 (or last best tolerated dose) of carfilzomib on Days 1, 2 and 15, 16
 
 
Lenalidomide
 
 
- Cycle 1-24 PO at 25 mg per dose (or at last best tolerated dose) on Days 1- 21
 
 
Dexamethasone
 
Dexamethasone will be administered between 30 minutes and 4 hours preceding carfilzomib (on days that they coincide), as follows:
 
 
• Cycles 1-4: 40 mg PO (subjects < 75 years) or 20 mg PO (subjects ≥ 75 years) per week
 
• Cycles 5-24: 20 mg PO per week
 
 
For weeks of daratumumab injection, dexamethasone dose is split into two doses: half the dose prior to daratumumab infusion and half the dose the day after.
 
Split weekly dosing on other days (e.g. 10 mg on Day 1 and 10 mg on Day 2, etc.) is permitted with approval from Lead Principal Investigator.
 
Dexamethasone given on days without carfilzomib (on Days 22 and 23 of Cycles 1-8) may be self-administered by the subject on an outpatient basis. If Day 2 of carfilzomib dosing is delayed (i.e., Day 2, 9, 16) 4 mg of dexamethasone premedication is required to be used prior to second treatment. Missed doses will not be replaced during a cycle. Missed doses of dexamethasone will not be made up.
 
Treatment Overview
 
Cycles 1 through 4 are considered D-KRd induction cycles, Cycle 5-8 are D-KRd consolidation, and cycles 9-24 D-KRd are maintenance cycles.
 
After Cycle 4, subjects who are deemed candidates for ASCT will proceed to stem cell harvest as per institutional guidelines. However, these subjects will not proceed straight to ASCT and will have cells frozen down for a potential future transplant at progression or unacceptable toxicity after
 |

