### **6.3 Study Drug Administration**

#### **6.3.1 Carfilzomib Administration**

Carfilzomib for injection is supplied as a lyophilized parenteral product in single-use vials. The lyophilized product is reconstituted with water for injection to a final carfilzomib concentration of 2.0 mg/mL prior to administration. The dose will be calculated using the subject's actual BSA at baseline. Subjects with a BSA  $> 2.2 \text{ m}^2$  will receive a dose based upon a  $2.2 \text{ m}^2$  BSA. Dose adjustments do not need to be made for weight gains/losses of  $\leq 10\%$ . Subjects with a Body Surface Area (BSA) of greater than  $2.2 \text{ m}^2$  will receive a capped dose of 44 mg of carfilzomib (at the  $20 \text{ mg/m}^2$  dose level), 59.4 mg of carfilzomib (at the  $27 \text{ mg/m}^2$  dose level), or 79.2 (at the  $36 \text{ mg/m}^2$  dose level).

Carfilzomib will be given as an IV infusion over 30 minutes on Days 1, 2, 8, 9, 15 and 16 of Cycles 1- 8 and Days 1, 2, 15 and 16 of Cycles 9-24, and must be administered prior to daratumumab. If the subject has a dedicated line for carfilzomib administration, the line must be flushed with a minimum of 20 mL of normal saline prior to and after drug administration. The dose will be administered at a facility capable of managing hypersensitivity reactions. Subjects will be pre-hydrated with 250mL normal saline or other appropriate IV fluid formulation on cycle 1 Day 1. Other hydration procedures will be optional and per the discretion of the treating investigator. Subjects will remain at the clinic under observation for at least 1 hour following each dose of carfilzomib in Cycle 1 and following the dose on Cycle 2, Day 1. Subjects should be monitored periodically during this period for evidence of fluid overload. Serum chemistry values, including creatinine, must be obtained and reviewed prior to each dose of carfilzomib during Cycles 1 and 2. Refer to [Table 6-8](#) for guidance regarding dose reduction in subjects with compromised renal function.

Doses of carfilzomib may be rescheduled up to 2 days if the scheduled day falls upon a holiday or with approval from the Lead Principal Investigator. If Day 2 of Carfilzomib dosing is delayed (i.e., Day 2, 9, 16) 4 mg of dexamethasone premedication is required to be used prior to second treatment. Missed doses will not be replaced during a cycle. Carfilzomib will be escalated from  $20 \text{ mg/m}^2$  (Cycle 1 Days 1 and 2)

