to 36mg/m^2 (Cycle 1 Days 8, 9, 15, 16 - see below) as long as the subject does not present with cytokine release symptoms (fever, rash, dyspnea, etc.) after Cycle 1 Day 2. If the subject does have concerning symptoms, they will be treated at 27mg/m^2 on Days 8 and 9 before being escalated to 36mg/m^2.

- Cycle 1: 20 mg/m^2 Days 1, 2; 36 mg/m^2 Days 8, 9, 15, 16. Alternatively, intermediate dose escalation (to 27mg/m^2 on Days 8, 9 of Cycle 1) will be allowed at the treating investigator's discretion.
- Cycle 2-8: 36 mg/m^2 (or best tolerated dose) Days 1, 2, 8, 9, 15 and 16
- Cycles 9-24: 36 mg/m^2 (or best tolerated dose) Days 1, 2, 15 and 16

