## 6.5 Dose-modification guidelines

The following sections and tables summarize dosing modifications of daratumumab, carfilzomib, lenalidomide and dexamethasone to manage possible toxicity. Dose modifications different from those stated in the protocol should be discussed with the Lead Principal Investigator. Administration of daratumumab, carfilzomib and lenalidomide will be discontinued in the event of any other toxicity that, in the opinion of the lead, secondary site, or treating investigator, warrants discontinuation.

In addition to dose reductions, administration of daratumumab, carfilzomib and lenalidomide will be held temporarily in the event of a treatment-related toxicity at the treating investigator's discretion.

Study treatment may be reintroduced if resolution of the event to the baseline value or to  $\leq$  Grade 1 within 21 days; otherwise study drug will be permanently discontinued. Any deviations from this plan must be approved by the Lead Principal Investigator.

All clinically-significant non-hematologic toxicities must be resolved to Grade 1 or baseline.

Individual dose modification of daratumumab is not permitted. Dosing can be delayed to manage daratumumab-related toxicities. Dose de-escalation of daratumumab will be based only on the Data and Safety Monitoring Board (DSMB) recommendation. Dose reduction levels of carfilzomib, lenalidomide and dexamethasone for toxicity management of individual subjects are provided below:

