| Hyperthyroidism or hypothyroidism                                                                                                                                                                                                                         | Omit lenalidomide for remainder of cycle, evaluate, and initiate appropriate therapy.

Restart lenalidomide next cycle at 1 dose decrement                                                                                                                                                                                  | No adjustment required                                                                                                                                                                                                                                                                                                          |
| Congestive heart failure (CHF)                                                                                                                                                                                                                                   | Any subject with symptoms of CHF, whether or not lenalidomide related, must have the dose held until resolution or return to baseline. If CHF was felt to be lenalidomide related, reinstate by one dose decrement after return to baseline. If no resolution of CHF after 2 weeks, the subject will be withdrawn from the study. | Any subject with symptoms of CHF, whether or not carfilzomib related, must have the dose held until resolution or return to baseline. If CHF was felt to be carfilzomib related, reinstate by one dose decrement after return to baseline. If no resolution of CHF after 2 weeks, the subject will be withdrawn from the study. |

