## 6.6 Treatment Discontinuation

Subjects will be free to discontinue treatment or withdraw from the study at any time, for any reason, or they may be withdrawn/ removed if necessary in order to protect their health (see reasons for withdrawal below).

Patients will be removed from further treatment for the following reasons:

- Disease Progression
- Non-compliance with study procedures
- Subject no longer consents to participate in the study
- Intercurrent illness that interferes with study assessments
- Treatment-related toxicity requiring treatment discontinuation
- Incidence or severity of AEs that indicates a potential health hazard to the subject
- For the fourth occurrence of the same Grade  $\geq 3$  non-hematological toxicity
- A delay in treatment > 21 days unless approved by the Lead Principal Investigator, or due to congestive heart failure unresolved for > 28 days the treatment shall be discontinued ([see Table 6-8](#))
- Treating investigator discretion
- Requirement for alternative therapy
- Suspected or positive pregnancy
- Termination of the study by the sponsor

The Lead Principal Investigator should be contacted regarding any impending discontinuation of a study subject. If the reason for withdrawal is the occurrence of an AE, the subject will be followed until such events resolve, stabilize, and, according to the treating investigator's judgment, there is no need for further follow up. The reason for withdrawal from study must be documented in the case report form.

Any Grade 5 toxicity related to study treatment will prompt stopping of the trial until further review is completed. Additionally, development of Grade 4 of non-hematologic toxicities in 2 or more patients will prompt the DSMB to stop the study for review to determine whether the trial should be terminated due to excessive toxicity.

In case of premature discontinuation of the study treatment, the investigations scheduled for the EOT should be performed, if possible. Should a patient decide to withdraw, every effort will be made to complete and report the observations as thoroughly as possible. The treating investigator should contact the patient to determine as completely as possible the reason for the withdrawal. A complete final evaluation at the time of the patient's withdrawal should be made, with an explanation of why the patient is withdrawing from the study.

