21. Peripheral blood and bone marrow aspirate samples collected at screening, end of cycle 8, time of response (to confirm complete response), end-of-treatment visit, and yearly after end of treatment for up to 2 years. Buccal mucosa swab will be collected at screening only.
22. AEs will be collected from the time of signing informed consent. 30 days following the last dose of D-KRD, patients will be considered to be off-study so no toxicities will be recorded following this period. All concomitant medications must be recorded on the concomitant medications case report form from 21 days before Day 1 through 30 days following the last dose of study drugs.
23. Assessment for disease progression in subjects who did not progress during treatment. At least every 3 months (+/- 30 days) for 5 years from safety follow-up visit (which must be 28days (+/- 3 days) post-last study treatment).
24. Lenalidomide must be prescribed through and in compliance with the Revlimid REMS® program of Celgene Corporation. Prescriptions must be filled within 7 days. Consideration should be given to prescribing lenalidomide 5 to 7 days in advance of Day 1 of each cycle to allow time for required patient and prescriber surveys, and drug shipment to patient. Any unused Revlimid® (lenalidomide) should be returned to the patient for disposition in accordance with the Revlimid REMS® program.
25. Cycles 1-8: Days 1, 2, 8, 9, 15 & 16. Cycles 9-24 Days 1, 2, 15 and 16.
26. Daily on Days 1-21 followed by a 7-day rest period every 28 days. On day coinciding with carfilzomib administration, lenalidomide should be taken at least 4 hours after the carfilzomib dose and may be self-administered at home by the subject. On days that carfilzomib is not administered, lenalidomide should be taken at approximately the same time each day.

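### Carfilzomib days in Cycles 5-8, the heart-failure stopping limit, and the dexamethasone dose at age 75 and over are each stated in two conflicting ways

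*Protocol*

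**What the plan says.** **Carfilzomib.** Section 4.1 of the protocol sets "carfilzomib on Days 1, 2, 8, 9, 15, 16 in Cycles 1-4 and Days 1, 2, 15, 16 in Cycles 5-8" and gives no carfilzomib days for Cycles 9-24. The synopsis gives, for Cycles 2-8, 36 mg/m2 "or last best tolerated dose) of carfilzomib on Days 1, 2, 8, 9 and 15, 16". Section 6.3.1 says infusions are given "on Days 1, 2, 8, 9, 15 and 16 of Cycles 1- 8 and Days 1, 2, 15 and 16 of Cycles 9-24", and its dose list repeats the six-day pattern for Cycles 2-8 ("or best tolerated dose) Days 1, 2, 8, 9, 15 and 16"). The Appendix 8 grid marks six carfilzomib days for Cycles 5-8, and footnote 25 reads "Cycles 1-8: Days 1, 2, 8, 9, 15 & 16. Cycles 9-24 Days 1, 2, 15 and 16".

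**Congestive heart failure.** Table 6-8, in both the lenalidomide and the carfilzomib columns, says "If no resolution of CHF after 2 weeks, the subject will be withdrawn from the study". Section 6.6 says that "due to congestive heart failure unresolved for > 28 days the treatment shall be discontinued" and refers the reader to Table 6-8. For toxicity in general, Section 6.5 allows treatment to restart if the event resolves "within 21 days; otherwise study drug will be permanently discontinued", with deviations subject to approval by the Lead Principal Investigator.

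**Dexamethasone.** The synopsis, Section 4.1 and Section 6.3.3 set the Cycle 1-4 weekly dose at 40 mg below age 75 and 20 mg from age 75. Appendix 8 footnote 27 states 40 mg weekly for those cycles with no age split.

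**The concern.** These are instructions that sites act on, and each exists in two incompatible forms.

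The carfilzomib conflict falls in the four cycles just before the primary assessment of stringent complete response and MRD negativity at the end of Cycle 8. That result is tested against a historical 30% rate from KRd without transplant at the same time point, so the exposure behind it should be stated one way.

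The CHF conflict concerns safety. Between day 15 and day 28 of unresolved heart failure, Table 6-8 requires withdrawal and Section 6.6 does not yet. The consequence differs as well: the table takes the patient out of the study, while Section 6.6 stops treatment. Read literally, the table's wording could end follow-up, although Section 6 follows patients removed from treatment for survival.

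The dexamethasone conflict would double the steroid dose in the patients for whom the protocol meant to halve it.

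There is also a recording problem. The protocol's overdose definition counts any oral amount above the specified dose, and any dosing more frequent than the required schedule. With two schedules in the text, six-day carfilzomib in Cycles 5-8 is an overdose under Section 4.1, and four-day dosing misses doses under Section 6.3.1.

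**Working it through.** The plan gives no figure of its own on this point. The conflicts are established by comparing the sections; the arithmetic only sizes them.

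**Carfilzomib**

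| Source | Cycles 5-8 | Cycles 9-24 |
|---|---|---|
| Section 4.1 | 4 days per cycle | not stated |
| Synopsis | 6 days | 4 days |
| Section 6.3.1, text and list | 6 days | 4 days |
| Appendix 8, grid and footnote 25 | 6 days | 4 days |

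Section 4.1 stands alone. It covers only 8 of the 24 cycles, leaving 24 - 8 = 16 without carfilzomib days. That suggests the two cycle labels are wrong, not that a different schedule was intended.

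Infusions through Cycle 8:
- Section 6.3.1: 6 × 8 = 48
- Section 4.1: 6 × 4 + 4 × 4 = 40
- Loss: 8/48 = 16.7%. Within Cycles 5-8 alone it is 16 against 24, one third fewer.

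Nominal cumulative dose through Cycle 8 with standard escalation (20 mg/m2 on two days, then 36 mg/m2):
- Cycle 1: 2 × 20 + 4 × 36 = 184 mg/m2
- Section 6.3.1: 184 + 7 × 6 × 36 = 1696 mg/m2
- Section 4.1: 184 + 3 × 6 × 36 + 4 × 4 × 36 = 184 + 648 + 576 = 1408 mg/m2
- Difference: 288 mg/m2; 288/1696 = 17.0%

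With the optional 27 mg/m2 step in Cycle 1:
- Cycle 1: 2 × 20 + 2 × 27 + 2 × 36 = 166 mg/m2
- Section 6.3.1: 166 + 1512 = 1678 mg/m2
- Section 4.1: 166 + 648 + 576 = 1390 mg/m2
- Difference: 288/1678 = 17.2%

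**Congestive heart failure**

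| Source | Limit | Consequence |
|---|---|---|
| Table 6-8 | 14 days | withdrawal from the study |
| Section 6.5 (toxicity in general) | 21 days | study drug stopped permanently |
| Section 6.6 | more than 28 days | treatment stopped |

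The limit in Section 6.6 exceeds that of the table it cites by 28 - 14 = 14 days, and exceeds the general limit by 28 - 21 = 7 days. As written, Section 6.6 allows longer for heart failure than for toxicity in general.

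**Dexamethasone, age 75 and over, Cycles 1-4**

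One weekly dose for 4 weeks × 4 cycles gives 16 weekly doses.
- Footnote 27: 16 × 40 = 640 mg
- Section 6.3.3: 16 × 20 = 320 mg
- Ratio: 2

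**The case against.** The strongest reply is that a careful reader can resolve all three. Section 4.1 is an overview, and the administration section, the synopsis and the study calendar all agree against it. Footnote 27 is silent on age, and a summary that omits an exception does not override three places that state it. On CHF the two rules can both be obeyed: the 28-day line is an outer limit, so withdrawing at 2 weeks breaches neither. Section 6.6 also allows removal at the treating investigator's discretion and asks that the Lead Principal Investigator be contacted about any impending discontinuation. Follow-up is unlikely to be lost, since Section 6.6 follows adverse-event withdrawals until the event resolves or stabilizes, and Section 6 provides survival follow-up. Finally, Section 6.3.5 says there will be no new starts, so the dosing corrections may reach few patients or none.

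Much of this stands. The carfilzomib and dexamethasone discrepancies look like slips, the dose differences are hypothetical, and the follow-up risk is small. The reply does not remove the conflicts. Section 6 directs readers to Appendix 8 for the treatment overview, so its footnotes are used in practice. Contacting the Lead Principal Investigator does not settle whether 14 or 28 days governs, and Section 6.6 contradicts the table it cites. The choice between them is clinical; the 2-week limit is preferred here because it is stricter and stands in the cited table.

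**Conclusion.** The concern holds: all three conflicts are in current operative text and should be corrected. If Section 4.1 were followed, a patient would receive 40 of 48 carfilzomib infusions before the primary assessment, about 17% less cumulative dose (17.0% with standard escalation, 17.2% with the intermediate step). The CHF limit differs by a factor of two, 14 against 28 days, and so does dexamethasone for patients aged 75 and over in Cycles 1-4, 320 against 640 mg.

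The dose figures assume nominal dosing with no reductions or missed doses, and that a site follows the outlying text. The protocol does not show that any patient was misdosed. Sample size, alpha and power are unaffected. The CHF rule matters most going forward, because it applies to anyone still on study treatment.

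**What to change.** 1. **Section 4.1.** Relabel the six-day carfilzomib schedule as Cycles 1-8 and the four-day schedule as Cycles 9-24. List the existing dosing records for Cycles 5-8 to see whether any patient was dosed by Section 4.1 as written.
2. **Section 6.6 and Table 6-8.** Use the 2-week CHF limit in both places unless the investigators justify the longer one. State one consequence in both: treatment discontinuation with continued follow-up, as Section 6 already provides.
3. **Appendix 8, footnote 27.** Add 20 mg dexamethasone weekly in Cycles 1-4 for patients aged 75 and over, matching Section 6.3.3.

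The cost is three text corrections in one clarifying amendment or site memo, plus one listing from data already collected. The dosing corrections change practice only for patients who have not passed Cycle 8 (carfilzomib) or Cycle 4 (dexamethasone), and the protocol does not say whether any remain.
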